### Sample size, power and statistical methods

The minimal clinically significant difference in length of hospital stay was thought to be greater than or equal to 12 hours. In order to perform the sample size calculation we determined mean duration of hospital stay and standard deviation (sd) from two available sets of admitted patients with bronchiolitis. Mean (sd) length of inpatient stay in a retrospective review of 36 patients admitted with bronchiolitis and requiring fluid replacement was 84 (49) hours. For the patients who were enrolled and randomised in the pilot study, mean (sd) duration of admission was 98 (70) hours, suggesting that patients who enter the study may have more severe illness.

Recruiting a total of 750 subjects (375 per arm) will give 80% power to detect an effect size of 0.2 (a small effect) using a two group t-test with a 0.05 two-sided significance level. That is a difference of 0.2 standard deviations between the mean length of stay in the 2 groups. If the sd is 70 hours (as in the pilot of the protocol), the study will be able to detect a difference between the groups of 14 hours; if the sd is 50 hours (as in the retrospective review), the study will be able to detect a difference of just over 8 hours. Thus, this study is powered to detect a difference in duration of admission of 14 hours, and possibly much less.

For the secondary outcomes, using this sample size, and knowing that approximately 30% of all intravenous cannulae have been shown to have complications,[25-28] gives 80% power to detect a 30% change in complications (from 30% to 20%) with a 0.05 significance level.

Analysis will be by intention to treat. Data will be analysed descriptively and statistically using the STATA data analysis program. Since this is a RCT and 2 of the outcome measures are measured on a continuous scale (duration of inpatient stay or hours of therapy), t-tests will be used to compare the 2 groups. If necessary due to skewed data, the data will be log-transformed. Data on parental satisfaction and complications will be treated as categorical and a Chi-squared test will be used.

No interim analysis of the data is planned.

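### The detectable difference quoted for an SD of 50 hours is about 8 hours, but the paragraph's own 0.2-SD rule gives 10 hours; the power statement should be restated, with the sample size unchanged

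*Protocol article*

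**What the plan says.** All of the relevant text is in the protocol article, section Sample size, power and statistical methods.

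- Threshold: "The minimal clinically significant difference in length of hospital stay was thought to be greater than or equal to 12 hours".
- Design statement: 750 patients, 375 in each arm, "will give 80% power to detect an effect size of 0.2". The test named is a two-sample t-test at a two-sided level of 0.05. The section then spells the effect size out: "That is a difference of 0.2 standard deviations between the mean length of stay in the 2 groups".
- Source data: a retrospective review of 36 patients had an SD of 49 hours, and the pilot had an SD of 70 hours. The section remarks that the pilot suggests trial entrants may be more severely ill.
- Conversion to hours: 14 hours if the SD is 70. If the SD is 50, which the section attributes to the retrospective review, "the study will be able to detect a difference of just over 8 hours".
- Conclusion: "Thus, this study is powered to detect a difference in duration of admission of 14 hours, and possibly much less".
- Complications: the same sample size "gives 80% power to detect a 30% change in complications (from 30% to 20"%), at the 0.05 level.

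**The concern.** The two conversions to hours appear in one sentence and should both be the 0.2-SD rule times an SD. The first is. The second is not, because 8 hours is 0.16 of an SD of 50. The concluding sentence draws on the second figure, so its numerical basis is wrong too.

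The power statement tells a reader what size of difference in length of stay the trial could reliably find. Someone who takes 8 hours at face value will think that the favourable case clears the 12-hour threshold by about 4 hours, when the margin is a little under 2 hours. In the unfavourable case (SD 70) the section's own 14 hours already lies above the threshold, and the power at 12 hours is not given.

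**Working it through.** **Inputs** (all from the sample size section): 375 per arm; two-sided alpha 0.05; 80% power; SD 70 (pilot), 50 (as used in the calculation) and 49 (as reported for the retrospective review); threshold 12 hours; complications 30% against 20%.

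**Formulae.** The detectable difference is SD × (1.960 + 0.842) × √(2/375), and √(2/375) = 0.0730. Power for a difference D is approximately Φ(D / (SD × 0.0730) − 1.960). The results were cross-checked with the noncentral t distribution.

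**1. The plan's general statement.** At 0.2 SD with 375 per arm, power is 78.2% (normal) or 78.1% (t). Exactly 80% needs 393 (normal) or 394 (t) per arm. The statement therefore holds to rounding. The exact 80%-power difference is 0.2046 SD (normal) or 0.2049 SD (t).

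**2. The figure at SD 70.** 0.2 × 70 = 14.0 hours; exact, 0.2049 × 70 = 14.3 hours. The plan's 14 hours reproduces.

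**3. The figure at SD 50.** 0.2 × 50 = 10.0 hours; exact, 0.2049 × 50 = 10.2 hours. With SD 49 the results are 9.8 and 10.0 hours. The plan's figure of a little over 8 hours does not reproduce.

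**4. Attempts to recover 8 hours at SD 50:**

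| Variant | Detectable difference |
|---|---|
| One-sided alpha 0.05, 80% power | 9.1 h |
| 750 per arm, 80% power | 7.2 h |
| One-sample formula, n = 375 | 7.2 h |
| Two-sided, 375 per arm, 60% power | 8.1 h |

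Under the 0.2-SD rule, 8 to 8.2 hours needs an SD of 40 to 41, and neither data set has that. No standard variant at 80% power gives the stated figure.

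**5. Power for 8 hours at SD 50.** 8 / (50 × 0.0730) = 2.19, and Φ(2.19 − 1.96) = 0.59. To reach 80% would take 614 (normal) or 615 (t) per arm.

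**6. Power for the 12-hour threshold, 375 per arm:**

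| SD | 12 / (SD × 0.0730) | Power |
|---|---|---|
| 70 | 2.35 | 65% |
| 50 | 3.29 | 91% |
| 49 | 3.35 | 92% |

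Power for 12 hours reaches 80% only if the SD is at most about 58.7 hours, from 12 / 0.2046. At SD 70 it would take about 536 per arm.

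**7. Effect on the conclusion.** The favourable case is (14 − 10) / 14 = 29% below 14 hours, rather than (14 − 8) / 14 = 43% below.

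**8. Side check on complications.** From 30% to 20% is a relative change of 10/30 = 33%. With 375 per arm its power is 88.7%, and about 294 per arm would give 80%. A true 30% relative change is 30% to 21%, and its power is 80.8%. This discrepancy errs on the safe side.

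**The case against.** The strongest reply is that the wrong number is only an illustration. The sample size was set from an effect size of 0.2, which stands to rounding, and the 14 hours at SD 70 is right. After correction the detectable difference at SD 50 is still below 12 hours, with 91% power at 12 hours. No patient, test or decision rule changes. All of this stands, and it is why the point is not graded higher.

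A reader might go further and infer that the plan conceals a lack of power for its own threshold. The text does not support that. The 14 hours at SD 70 is printed in the same section as the 12-hour threshold, and the section nowhere claims 80% power for 12 hours at that SD. It says that entrants may be more severely ill, but it presents both SDs without choosing one. The 65% is thus one end of a range and not the trial's established power. Omitting the power at 12 hours is a gap in presentation that is worth filling in the same edit.

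Whether the closing clause of the conclusion is too strong is partly judgement, since a difference below 14 hours is indeed detectable if the SD is nearer 50. The clause should therefore be made specific and not simply struck out.

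A reader might also want a rule that a non-significant result be judged by whether its confidence interval excludes 12 hours either way. That would be a new criterion and would correct no stated figure. It would also not carry over directly if length of stay is log-transformed, which the section allows. It is not part of this point.

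On complications, the stated power is conservative and the endpoints are explicit, so no inference is harmed. It is a side note only.

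**Conclusion.** The figure of a little over 8 hours at SD 50 is wrong as written. The paragraph's own rule gives 10 hours, and the exact value is 10.2 hours at 80% power with 375 per arm. Power for 8 hours at that SD is 59%. The concluding sentence leans on the wrong figure and should be tied to the right one. Power for the 12-hour minimal difference runs from 65% (SD 70) through 91% (SD 50) to 92% (SD 49).

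These results assume 375 analysed per arm, a common SD, a two-sided 0.05 two-sample t-test on untransformed hours, and an SD within the range that the section gives.

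This is a should-fix restatement of a stated power figure for the primary endpoint. It does not show that the trial is too small for its stated effect size, and it gives no reason to change the 750.

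**What to change.** Keep 750 patients and restate the paragraph:

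- 375 per arm gives 80% power for about 0.205 SD, that is about 14.3 hours at an SD of 70 or about 10.2 hours at an SD of 50.
- Power for the 12-hour minimal difference is 65% at SD 70, 91% at SD 50 and 92% at SD 49.
- In the concluding sentence, replace the final clause, which suggests a far smaller detectable difference, with: or about 10 hours if the SD is 50.
- As a side note, give the complication figure either as 89% power for 30% to 20% (a 33% relative change) or as 81% power for 30% to 21% (a 30% relative change).

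The cost is wording only: no extra patients and no change to the test or the analysis. The stated figure for the favourable SD becomes less favourable, and the complication figure for 30% to 20% becomes more so.

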### Study Design and setting

This study is an open randomised trial comparing two interventions. This study will take place in 6 paediatric emergency departments and inpatient wards in Australia and New Zealand.

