### Patient randomisation

The patients will be randomised at the time they require non oral fluid replacement. Randomisation will be stratified by 2 age groups (2 months to less than 6 months, 6 months to less than 12 months) and by site. Randomisation will be blocked in 3 randomly allocated block sizes to ensure concealment of allocation. Each site will have its own set of opaque sealed randomisation envelopes. These will have a reminder of inclusion and exclusion criteria to be assessed before the envelope is opened.

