#### Clinical observations from nursing records

SpO_2_, respiratory rate, respiratory effort, and heart rate will be measured at enrolment, at hourly intervals for the first 2 hours then 2 hourly. These will allow comparison of groups by severity of disease at enrolment, and ensure any clinically relevant complications are captured.

Oxygen administered (L/min for nasal cannulae or %O_2 _for head box) will be documented for each shift. The times oxygen is commenced and ceased will be documented. This will allow accurate capture of the duration of oxygen therapy. Type, route and volume of fluid administered will be recorded, with hourly, shift, and daily totals. This allows assessment of fluid requirements and cross referencing volumes of fluid infused. Hydration status of the patients will be measured using urine output (with shift and daily totals) and weight (measured at the time of admission, and then daily).

Complications recorded will include: episodes of apnoea and bradycardia (lasting more than 20 seconds); all episodes where the SpO_2 _was recorded at < 90%; and the need for replacement of, or problems with the IV cannula or NGT.

The need for and duration of ICU admission will be documented. Duration of hospital admission will be documented and checked by calculation from the hospital admissions and discharge system.

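### Randomisation is stratified by site and age group, but the stated tests ignore the strata; to the extent that the strata predict length of stay, the primary test is conservative and loses some power

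*Protocol article*

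**What the plan says.** Under Patient randomisation, the protocol article states "Randomisation will be stratified by 2 age groups" and then adds site as the second factor: "6 months to less than 12 months) and by site". It also states "Randomisation will be blocked in 3 randomly allocated block sizes". Study Design and setting gives the number of sites: "This study will take place in 6 paediatric emergency departments". Six sites by two age groups makes 12 strata.

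Under Sample size, power and statistical methods, the continuous outcomes (duration of stay and hours of therapy) are handled as follows: "t-tests will be used to compare the 2 groups". There is one proviso: "If necessary due to skewed data, the data will be log-transformed". Complications and parental satisfaction go to a chi-squared test. The Abstract names the same two tests, and the sample size is built on the same two-group t-test. No section carries site or age group into an analysis.

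Under Clinical observations from nursing records, oxygen saturation, respiratory rate, respiratory effort and heart rate are recorded at enrolment and at intervals afterwards. Of these the article says "These will allow comparison of groups by severity of disease at enrolment", and it also gives them a role in capturing complications.

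**The concern.** Blocking within site and age group keeps the two arms close to equal in every stratum. Differences in mean stay between strata then contribute almost nothing to the difference between arms. A plain t-test does not know this. It estimates its error from the total within-arm variance, which includes the between-stratum part. If the strata matter for length of stay, the reported standard error is larger than the true one, the confidence interval is too wide, and the null hypothesis is rejected less often than the nominal 5%.

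What is at stake is efficiency. The trial has little power to spare at its own design effect, and the remedy needs no further patients or data. The protocol does not leave the method open for a later analysis plan: it names a test that does not follow its own randomisation.

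**Working it through.** **Inputs from the article.** 375 per arm; effect 0.2 SD (14 hours if the SD is 70 hours); two-sided 5%; two-group t-test; 6 sites × 2 age groups = 12 strata, blocked.

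**Input not in the article.** R², the share of length-of-stay variance lying between the 12 strata. It is assumed at 0, 0.02, 0.05, 0.10 and 0.20.

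**Step 1: the stated power.** Expected test statistic = 0.2 × √(375/2) = 2.739. Power = Φ(2.739 − 1.960) = Φ(0.779) = 78.2% (78.1% with the exact noncentral t). This is close to the stated 80%. A full 80% would need 2 × (1.960 + 0.842)² / 0.2² ≈ 393 per arm, 786 in total.

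**Step 2: the effect of ignoring the strata.** Let the total within-arm SD be 1. With near-perfect balance within strata:

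- True standard error of the arm difference: √(1 − R²) × √(2/375).
- Standard error used by the t-test: √(2/375). It is too large by the factor 1/√(1 − R²).
- True type I error of the t-test: 2 × [1 − Φ(1.960/√(1 − R²))].
- Power of the t-test: Φ((2.739 − 1.960)/√(1 − R²)).
- Power with adjustment for strata: Φ(2.739/√(1 − R²) − 1.960).

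Example at R² = 0.05, where √0.95 = 0.9747:

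- Type I error: 1.960/0.9747 = 2.011, giving 4.4%.
- Unadjusted power: Φ(0.779/0.9747) = Φ(0.799) = 78.8%.
- Adjusted power: Φ(2.810 − 1.960) = Φ(0.850) = 80.2%.

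| Assumed R² (all between strata) | SE overstated by | True type I error, t-test | Power, t-test | Power, adjusted | Total N for 80%, adjusted |
|---|---|---|---|---|---|
| 0 | 0% | 5.0% | 78.2% | 78.2% | 786 |
| 0.02 | 1.0% | 4.8% | 78.4% | 79.0% | 770 |
| 0.05 | 2.6% | 4.4% | 78.8% | 80.2% | 746 |
| 0.10 | 5.4% | 3.9% | 79.4% | 82.3% | 708 |
| 0.20 | 11.8% | 2.8% | 80.8% | 86.5% | 628 |

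**Step 3: check by simulation.** 750 patients in 12 strata of unequal size, permuted blocks (sizes 2, 4 and 6 assumed, since the article does not give them), normal outcomes, 6,000 replicates per scenario. Adjustment was for all 12 strata.

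| R² | Null rejection, t-test vs adjusted | Power, t-test vs adjusted |
|---|---|---|
| 0 | 0.048 vs 0.047 | 77.7% vs 77.8% |
| 0.05 | 0.047 vs 0.053 | 79.5% vs 80.8% |
| 0.10 | 0.040 vs 0.051 | 78.6% vs 81.5% |
| 0.20 | 0.030 vs 0.051 | 80.8% vs 86.3% |

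Simulation error is about 0.3 points for the rejection rates, √(0.05 × 0.95/6000), and 0.5 points for power, √(0.8 × 0.2/6000). The results agree with the formulas within that error.

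**The case against.** The strongest reply is that nothing here threatens validity. The t-test estimate is unbiased, its type I error is at or below 5%, and the sample size was computed for that same test. All of this stands. A reader might infer from a type I error that differs from 5% that the trial risks a false positive. By this route it does not.

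The second reply is that the size rests on an R² the article does not supply. This also stands. A reader might take it as established that stay depends on site, age and severity, but the article only makes this plausible:

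- Background reports large differences in management between hospitals.
- Outcome measures says administrative and social factors affect stay, without tying them to site.
- The remark on a more severe course, under Inclusion and Exclusion Criteria, concerns infants under 8 weeks, who are excluded.

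Nothing in the article supports strata explaining as much as 20%. At 0.02 the gain is 0.6 points of power, and at 0 there is none.

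Third, a reader might extend the argument to the enrolment observations. They are not stratification factors. For variance that they explain, the t-test has the right size and its standard error is not overstated, so they do not belong in the R² above. Nor does the article confine them to description. Leaving them out of the model is not an error.

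Fourth, adjustment does not repair power at the 12-hour minimal difference. With an SD of 70 hours the expected statistic is (12/70) × √(375/2) = 2.347, giving Φ(0.387) ≈ 65% unadjusted. Adjusted power is about 67%, 70% and 75% at R² of 0.05, 0.10 and 0.20. That shortfall is a separate sample-size matter.

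**Conclusion.** The point holds as one of efficiency. The protocol stratifies by site and age group and then names tests that ignore both. If the strata predict length of stay, the t-test is conservative.

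For R² from 0 to 0.10, adjustment adds between 0 and about 3 points of power, and the true type I error of the t-test falls from 5.0% to 3.9%. At R² of 0.20 the gain is nearly 6 points and the type I error is 2.8%. At about 0.05, adjustment brings the planned 750 patients up to the stated 80%.

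Both the type I errors and the powers assume that all of R² lies between strata, that balance within strata is close, and that the outcome is analysed on the scale to which R² refers. The mismatch is certain from the text; its size is not known. The change is worth making because the possible loss is avoidable and, with 750 patients, adjusting costs essentially nothing if the strata turn out not to matter.

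**What to change.** Pre-specify the following:

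- **Primary analysis.** Linear regression of length of stay on arm with site and age group as covariates (5 + 1 extra parameters), reporting the adjusted mean difference in hours with a 95% CI. If the log-transform provision is invoked, fit the same model to log length of stay and report the effect as a ratio with its 95% CI. Additive site and age terms recover the full gain shown if the age difference is similar across sites.
- **Complications.** Mantel-Haenszel analysis stratified by site and age group.
- **Sensitivity.** Keep the t-test and chi-squared test as unadjusted analyses.
- **Optional.** Adjust also for one named enrolment severity variable, such as oxygen saturation, fixed in advance. This may add power; it does not correct the size of the test.

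The cost is a change of wording and a few lines of Stata code. Site and age group are known from randomisation, and oxygen saturation is already recorded at enrolment. The Discussion reports just over 190 patients randomised and no interim analysis is planned, so the change could still be specified before the outcome data are compared.

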**Methods/Design:**

A prospective randomised multi-centre trial in Australia and New Zealand where children between 2 and 12 months of age with bronchiolitis, needing non oral fluid replacement, are randomised to receive either intravenous (IV) or nasogastric (NG) rehydration.

750 patients admitted to participating hospitals will be recruited, and will be followed daily during the admission and by telephone 1 week after discharge. Patients with chronic respiratory, cardiac, or neurological disease; choanal atresia; needing IV fluid resuscitation; needing an IV for other reasons, and those requiring CPAP or ventilation are excluded.

The primary endpoint is duration of hospital admission. Secondary outcomes are complications, need for ICU admission, parental satisfaction, and an economic evaluation. Results will be analysed using t-test for continuous data, and chi squared for categorical data. Non parametric data will be log transformed.

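### The 12-hour target and the sample size are set in mean hours, but the primary t-test may move to the log scale, where it compares geometric means and no target is stated

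*Protocol article*

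**What the plan says.** The section on sample size, power and statistical methods sets the target in absolute hours: "The minimal clinically significant difference in length of hospital stay was thought to be greater than or equal to 12 hours". It sizes the trial at 375 per arm "using a two group t-test with a 0.05 two-sided significance level" and explains the effect size in these words: "That is a difference of 0.2 standard deviations between the mean length of stay in the 2 groups". The planning data come from two patient sets. In the randomised pilot, "mean (sd) duration of admission was 98 (70) hours"; in a retrospective review of 36 patients, stay among those "requiring fluid replacement was 84 (49) hours".

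The same section names the t-test for the two duration outcomes and adds: "If necessary due to skewed data, the data will be log-transformed". The abstract has its own version: "Non parametric data will be log transformed". Neither place gives a target ratio for the log scale or a route back to mean hours.

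**The concern.** A t-test on hours asks whether mean stay differs. A t-test on log hours asks whether geometric mean stay differs. The two questions coincide only under extra conditions, such as a purely proportional effect with equal spread on the log scale. The article sets its clinical threshold and its power on the first question, then allows the primary test to answer the second.

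If the switch is likely, the stated power describes an analysis that will probably not be the primary one. A significant result would then be a ratio with no stated threshold to set it against, and in some trials the verdict would depend on the scale used.

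**Working it through.** **Inputs.** From the sample size section: 375 per arm, two-sided 0.05, 0.2 SD, 12 h, mean (SD) 98 (70) and 84 (49). Assumed here, because the article gives only means and SDs: lognormal stays, with gamma as a second shape.

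**1. The plan's own figure.** Power = Φ(0.2/√(2/375) − 1.96) = Φ(2.739 − 1.960) = 78%, close to the stated 80%. The effect detectable with 80% power is (1.960 + 0.842) × √(2/375) = 0.2046 SD, or 14.3 h at SD 70. The figure holds on the scale of mean hours, which is the scale the text describes.

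**2. Is skew foreseeable?** The coefficients of variation (CV) are 70/98 = 0.71 and 49/84 = 0.58. Two SDs below the mean is 98 − 140 = −42 h and 84 − 98 = −14 h, which a length of stay cannot be. In simulated trials with lognormal or gamma stays, a formal skewness test called for the log in essentially 100%.

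**3. What the log scale does to 12 hours.** For lognormal data, log-variance = ln(1 + CV²) and geometric mean = mean × exp(−log-variance/2).
- 98 (70): log-SD 0.642, geometric mean 79.7 h. A 12 h fall in the mean is a ratio of 86/98 = 0.878, or 9.8 h between geometric means.
- 84 (49): log-SD 0.541, geometric mean 72.6 h. The ratio is 72/84 = 0.857, or 10.4 h between geometric means.

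So no single ratio stands for 12 hours.

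**4. Is the switch needed for validity?** With identical arms and 375 per arm (20,000 simulations), the t-test on hours rejects in 5.4% (lognormal 98/70) and 4.8% (lognormal 84/49). A skewness rule blind to arm rejects in 4.9% and 5.1%. Taking the smaller of the two p-values gives 6.6% to 7.3% across the lognormal and gamma cases.

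**5. Does the scale change the answer?** For a true 12 h reduction at constant CV:

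| Shape, baseline | Power on hours | Power on logs | Tests disagree |
|---|---|---|---|
| Lognormal, 98 (70) | about 71% | 80% | 13% |
| Gamma, 98 (70) | 71% | 60% | 17% |
| Lognormal, 84 (49) | 95% | 97% | 3% |
| Gamma, 84 (49) | 95% | 91% | 6% |

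**6. Illustration: equal means, unequal spread.** Both arms have mean 98 h with lognormal stays, and one arm has SD 70 (geometric mean 79.7 h). The log test has z = ln(ratio of geometric means)/√((s₁² + s₂²)/375), where s₁ and s₂ are the log-SDs.

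| Other arm | Log-SD | Geometric mean | z | Log test rejects | Welch test on hours |
|---|---|---|---|---|---|
| SD 63 | 0.588 | 82.4 h | 0.74 | 11% (12% simulated) | 5% |
| CV 0.58 (SD 57.2) | 0.541 | 84.7 h | 1.38 | 28% (27% simulated) | 5% |
| SD 49 (CV 0.50) | 0.472 | 87.7 h | 2.30 | 63% | 5% |

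The reverse also occurs: with equal geometric means and arithmetic means 12 h apart (98 and 110 h), the log test rejects in 4.9% and the test on hours in 45%.

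**The case against.** The strongest reply is that the alternative scale is named in advance with its reason, that what triggers it is ordinary content for an analysis plan not shown here, and that the primary aim speaks of duration of admission without naming the mean. Either scale would be defensible if fixed. Much of this stands, and the absent trigger is not the point made here. What remains is a rule the article does state, which moves the primary test off the scale on which the same section defines its target and its power. The likelier the switch, the less the data choose the test, but the more the stated power belongs to another analysis.

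Four stronger readings are tempting and are not supported.
- **Inflated type I error.** A reader might infer it from a data-dependent choice in an open trial. Step 4 shows about 5% for a rule blind to arm. The rise to about 7% requires choosing by result, and nothing in the article says that will happen.
- **A 63% false-positive rate.** The SDs 70 and 49 come from two different patient sets and not from two arms, and putting 49 on a mean of 98 gives a CV of 0.50 that appears nowhere in the article. With the article's own CVs the figure is 27% to 28%. None of these is a false-positive rate, because the medians do differ. Nothing in the article suggests that route of hydration changes spread but not the mean.
- **A distorted economic evaluation.** It is a separate decision-tree analysis, and a log transformation for the t-test does not alter its inputs.
- **Hours lost from the report.** The data will also be summarised descriptively, so hours can still be shown. They would not carry the primary test.

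**Conclusion.** The point holds as a mismatch of scale. The target and sample size concern mean hours; the rule as written would probably make the primary test a comparison of geometric means without a target. At 375 per arm skew of this size does not require that move.

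The practical size is moderate: the two tests disagree on significance in about 13% of trials with a true 12 h reduction from 98 (70) h, assuming lognormal stays and constant CV. It is 17% under gamma stays, and 3% to 6% if the 84 (49) data are the better guide. The equal-mean figures of about 12%, 27% and 63% show only that the two tests answer different questions. All simulated figures rest on assumed shapes.

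**What to change.** In the sample size, power and statistical methods section, name the difference in arithmetic mean hours with its 95% CI as the primary analysis whatever the skew, using an unequal-variance or robust standard error and adjusting for the stratification factors, site and age group. Report the log-scale ratio of geometric means as a pre-specified sensitivity analysis that cannot replace it. Rewrite the abstract sentence to match; the term it uses describes methods, not data.

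The cost is wording, with no change to the 750. The price in power depends on shape: for 12 h from 98 (70) h, about 71% instead of 80% if stays are lognormal with a proportional effect, but about 71% instead of 60% if they are gamma-shaped. The article reports recruitment still under way, with just over 190 randomised and no interim analysis planned, so on its own account the scale could still be fixed before outcomes are compared.

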##### For both groups

All patients will be admitted to the ward under the appropriate unit. Total fluid replacement will not exceed 100% of normal daily requirements. Oral feeds will be at the discretion of the clinical team and the IV or NG fluid rate adjusted accordingly.

A parent satisfaction score will be obtained using a standardised, five point Likert scale. The score will be obtained daily from one parent or by agreement with both parents if they are in attendance. A final "overall" satisfaction score will be obtained immediately prior to hospital discharge.

All patients will be followed up at 5 to 7 days post discharge with a standard questionnaire to determine the incidence of complications, or need for further medical care.

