### Outcome measures

The primary outcome measure is the inpatient length of stay. This will be recorded in 2 ways: 1) the actual duration of inpatient stay will be determined from the computerised database of patient admission; 2) Given that the length of stay can be affected by many administrative and social factors unrelated to the condition of the child, we will record and report also the time until the child is ready for discharge using objective criteria. An infant will be considered ready for discharge if he/she has not received supplemental oxygen for 12 hours, has had stable respiratory status for 4 hours (including slight or nil recession) and is feeding adequately.

The secondary outcome measures are the incidence and type of complications of hydration therapy (complications will include any adverse event related to the method of hydration, including but not limited to electrolyte abnormalities, IV line/NGT needing replacement, infection, thrombosis of the IV site, trauma to the nose from the NGT, pulmonary aspiration, extravasation of IV fluid); the duration of therapy; parental satisfaction (measured daily) and an economic appraisal of each intervention.

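### The five-point parental satisfaction score is ordinal but is assigned an unordered chi-squared test, and the score to be tested (daily or overall) is not named

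*Protocol article*

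**What the plan says.** Protocol article, 'For both groups': "A parent satisfaction score will be obtained using a standardised, five point Likert scale". The same section sets the frequency: "The score will be obtained daily from one parent or by agreement with both parents if they are in attendance". It then adds a final overall rating: "satisfaction score will be obtained immediately prior to hospital discharge".

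'Outcome measures' lists among the secondary outcomes "parental satisfaction (measured daily) and an economic appraisal of each intervention", with no mention of the overall score.

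'Sample size, power and statistical methods' names the test: "Data on parental satisfaction and complications will be treated as categorical and a Chi-squared test will be used". The abstract agrees: "Results will be analysed using t-test for continuous data, and chi squared for categorical data". No trend or ordinal version is named, the score entering the test is not identified, and no effect size or power is given for satisfaction.

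**The concern.** The five categories run from worse to better. A Pearson chi-squared test on a 2×5 table spreads its sensitivity over 4 degrees of freedom and gives the same p-value if the categories are shuffled. It asks whether the two distributions differ in any way. The stated secondary aim is the difference in satisfaction between the treatments, which is most naturally answered by one signed estimate with an interval.

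A second point depends on which score is used. The outcome list describes satisfaction as measured daily, yet a single overall score per family also exists. If the daily scores were put into one table, several scores from the same family would be counted as independent. Families with longer stays would also contribute more of them, and length of stay is the primary outcome on which the arms are hypothesised to differ.

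**Working it through.** The protocol gives no power figure for satisfaction, so there is none to reproduce. From the document: 375 per arm ("Recruiting a total of 750 subjects (375 per arm) will give 80% power to detect an effect size of 0.2 (a small effect", stated for the primary outcome), two-sided 0.05, and mean stays of 84 h (sd 49) and 98 h (sd 70). Assumed, because the document gives none: the score distributions, the odds ratios and the within-family correlations.

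**1. One score per family, consistent shift**

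Control p = 3/7/15/40/35%, with cumulative proportions 3/10/25/65%. Dividing the cumulative odds by the odds ratio (OR) gives the shifted arm q:
- OR 1.4: 2.2/5.2/11.9/37.8/43.0%
- OR 1.5: 2.0/4.9/11.3/37.1/44.7%

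Chi-squared, 4 df, critical value 9.49, noncentrality λ = n Σ (p−q)²/(p+q):
- OR 1.4: λ = 375 × 0.01647 = 6.18, power 48%
- OR 1.5: λ = 8.92, power 66%

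Rank test: θ = P(q-arm score higher) + ½P(tie); SE = √[(1−Σm³)/12 × 2/375], with m = (p+q)/2:
- OR 1.4: θ = 0.549, SE = 0.0198, z = 2.49, power Φ(2.49−1.96) = 70%
- OR 1.5: θ = 0.559, SE = 0.0197, z = 2.99, power 85%

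Simulation (4,000 trials per scenario) agrees: 47.6% v 69.9% at OR 1.4, 66.6% v 85.1% at OR 1.5, and 5.4% v 5.0% at OR 1.0. Both tests therefore hold their size.

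**2. Other assumed distributions** (2/5/13/40/40%, uniform, and 2/3/5/25/65%; 3,000 simulated trials each)

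| OR | Chi-squared | Wilcoxon |
|---|---|---|
| 1.3 | 23–31% | 40–52% |
| 1.45 | 45–62% | 67–82% |
| 1.6 | 65–85% | 86–95% |

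Within each distribution the loss is about 10 to 22 percentage points.

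**3. Differences that are not a shift** (same control, 375 per arm, same formulas)
- 7/8/15/32/38%: λ = 10.05, chi-squared 72%; θ = 0.490, rank test 8%
- 8/7/15/35/35%: λ = 9.77, chi-squared 70%; θ = 0.478, rank test 19%

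Simulations gave 73–75% v 8% and 72% v 18–19%. The ranking reverses.

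**4. If daily scores were pooled**

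Mean stay implies 84/24 = 3.5 to 98/24 = 4.1 scores per family. In a latent-normal model with no true difference (3 days, 4 days, or variable stay with mean 84 h and sd 49 h; 2,000 simulated trials each), the type I error of the pooled chi-squared was:

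| Within-family correlation | Type I error |
|---|---|
| 0 | 4–6% |
| 0.3 | 8–12% |
| 0.5 | 12–20% |
| 0.7 | 19–32% |

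With one score per family in the same model it stayed at 4–5%.

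**The case against.** Five things can be said for the plan.

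- **The test is valid.** With one score per family it keeps about 5% type I error. This stands: the loss is in efficiency and interpretation.
- **The power gap depends on the alternative.** A proportional-odds shift is close to the best case for a rank test, and step 3 shows the reverse. This stands. Mixed patterns are conceivable, since the Background describes different possible drawbacks for each route. The power claim therefore needs its condition.
- **Five categories and 4 df are inferred.** The wording would also allow collapsing to satisfied or not. That would give a direction but would not recover the power. Taking the top two categories at OR 1.4, control 75% has odds 3, and 3 × 1.4 = 4.2 gives 80.8%. Then z = 0.0577/√(2 × 0.779 × 0.221/375) = 1.90, which is about 48% power.
- **Direction can be read from the proportions.** The protocol also promises descriptive analysis. This is partly right, but it is no substitute for an estimate with an interval.
- **The choice of score may sit in the full protocol or SAP.** This stands as far as silence on repeated scores goes. The chi-squared test itself, however, is a stated choice and not an omission.

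A reader might infer from the outcome list that the daily scores will be pooled, so that the satisfaction p-value will be too small. The document does not support that. The words on daily measurement may only describe collection, no section says the daily scores are tabulated together, and one overall score per family is available.

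**Conclusion.** The point holds as a minor one. An ordinal score is assigned a test that ignores its order and gives no single directional estimate. Under a consistent shift at OR 1.4 to 1.5, the cost is about 19 to 22 percentage points of power with the assumed 3/7/15/40/35% distribution. It is about 10 to 22 points over the other distributions and odds ratios tried. These figures show size only, because the protocol gives no satisfaction distribution, and the advantage does not extend to differences that are not a shift.

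The independence problem is conditional: it arises only if daily scores are pooled, which the document does not state. It would be wrong to conclude that the planned test is invalid, that it loses power against every alternative, or that the complications analysis must change. The primary outcome and its conclusion are unaffected.

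**What to change.** Name the overall discharge score as the tested satisfaction outcome. Compare arms with an ordinal method: proportional-odds regression with terms for site and age group (the randomisation strata), or a Wilcoxon test stratified by them. Report a common odds ratio with 95% CI alongside the category proportions by arm. Show the daily scores descriptively, or in a model that accounts for repeated scores per family.

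The cost is wording in the analysis plan. The overall score is already collected, and no extra patients or data are needed. Recruitment was still under way when the article was written, so the choice can be fixed before outcome data are examined, which matters for a subjective outcome in an open trial. The downside is lower sensitivity to differences that are not a shift; the category proportions by arm would show these.
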